## LIST OF ABBREVIATIONS AND RELEVANT DEFINITIONS

|                         |                                                                                                                                                                                                                                                                                                                                                  |
|-------------------------|--------------------------------------------------------------------------------------------------------------------------------------------------------------------------------------------------------------------------------------------------------------------------------------------------------------------------------------------------|
| AE               | Adverse Event                                                                                                                                                                                                                                                                                                                             |
| CCMO             | Central Committee on Research Involving Human Subjects; in Dutch: Centrale Commissie Mensgebonden Onderzoek                                                                                                                                                                                                                               |
| COD              | Check-up On Demand                                                                                                                                                                                                                                                                                                                        |
| FU               | Follow-Up                                                                                                                                                                                                                                                                                                                                 |
| GCP              | Good Clinical Practice                                                                                                                                                                                                                                                                                                                    |
| GDPR             | General Data Protection Regulation; in Dutch: Algemene Verordening Gegevensbescherming (AVG)                                                                                                                                                                                                                                              |
| HCP              | Healthcare Provider                                                                                                                                                                                                                                                                                                                       |
| IB               | Investigator's Brochure                                                                                                                                                                                                                                                                                                                   |
| IC               | Informed Consent                                                                                                                                                                                                                                                                                                                          |
| IMDD             | Investigational Medical Device Dossier                                                                                                                                                                                                                                                                                                    |
| METC             | Medical research ethics committee (MREC); in Dutch: medisch-ethische toetsingscommissie (METC)                                                                                                                                                                                                                                            |
| Review Committee | Medical research ethics committee (MREC) or CCMO                                                                                                                                                                                                                                                                                          |
| RFU              | Routine Follow Up                                                                                                                                                                                                                                                                                                                         |
| (S)AE            | (Serious) Adverse Event                                                                                                                                                                                                                                                                                                                   |
| SF               | Short Form                                                                                                                                                                                                                                                                                                                                |
| Sponsor          | The sponsor is the party that commissions the organisation or performance of the research, for example a pharmaceutical company, academic hospital, scientific organisation or investigator. A party that provides funding for a study but does not commission it is not regarded as the sponsor, but referred to as a subsidising party. |
| THA              | Total Hip Arthroplasty                                                                                                                                                                                                                                                                                                                    |
| TKA              | Total Knee Arthroplasty                                                                                                                                                                                                                                                                                                                   |
| UAVG             | Dutch Act on Implementation of the General Data Protection Regulation; in Dutch: Uitvoeringswet AVG                                                                                                                                                                                                                                       |
| WMO              | Medical Research Involving Human Subjects Act; in Dutch: Wet Medisch-wetenschappelijk Onderzoek met Mensen                                                                                                                                                                                                                                |

### SUMMARY

**Rationale:** Clinical guidelines recommend routine follow up (RFU) with X-ray and clinical visit at 1 year after Total Hip Arthroplasty (THA) and Total Knee Arthroplasty (TKA). However, evidence for (cost-)effectiveness of RFU is lacking. Registry data show excellent survival of THA and TKA and the added value of RFU can be questioned, as revisions are rare and seldom without symptoms. However, replacing RFU with a final follow up within 3 months and thereafter only check-ups on demand (COD), could lead to risks such as missed complications, lower patient satisfaction, or decreased physical function.

**Objective:** To investigate the (cost-)effectiveness of COD compared to RFU at 1 year, up to 2 years after THA and TKA.

**Study design:** A hybrid effectiveness (de-)implementation trial type II, with a stepped-wedge cluster trial design.

**Study population:** Patients scheduled for THA or TKA who experience pain and disability in the knee or hip joint due to osteoarthritis, and aged  $\geq 50$  years at the time of the surgery.

**Intervention:** Check-up on demand (COD) by the patient or healthcare provider (HCP), after a final clinical visit with X-ray within 3 months to diagnose complications and provide instructions when to contact an HCP.

**Comparator:** Routine follow up (RFU) consisting of an X-ray and clinical visit within 3 months and at 1 year after surgery. Patients are welcome to contact an HCP in case of pain, concerns or other symptoms associated with their prosthesis at any time.

**Main study parameters/endpoints:** The main study parameters are clinical and process outcomes. The clinical outcome is patient-reported physical function, measured with the PROMIS questionnaire, 2 years after surgery (1 year after RFU or COD). The process outcome is healthcare consumption, including X-rays and clinical visits.

**Nature and extent of the burden and risks associated with participation:** In the RFU group, the burden involves a hospital visit for an X-ray and clinical visit. In the COD group, the burden is lower, as participants attend follow-up visits only if necessary. However, there is a small risk of missed complications. This risk is considered minimal due to the low occurrence of asymptomatic complications. Studies and clinical practice show that when complications occur without pain, patients often do not take action, or this can lead to overdiagnosis and overtreatment. Participants will complete questionnaires pre-operative, 1 year after THA or TKA, 15, 18 and 24 months after THA or TKA. This burden is minimal, as only essential questions are included, developed in collaboration with patient representatives. Patient interviews showed no concerns about participation in this study.

### 1. INTRODUCTION AND RATIONALE

Total Hip Arthroplasty (THA) and Total Knee Arthroplasty (TKA) are two of the most common procedures for patients suffering from osteoarthritis and other degenerative joint diseases. These surgeries are highly effective in reducing pain and improving mobility. In 2022, more than 36,700 THAs and 26,700 TKAs were implanted (1,2), with osteoarthritis being the primary indication in 86% and 97% of cases, respectively (3,4). Given the growing elderly population and rising demand for these surgeries, the need for optimized follow up care has become increasingly important.

Current clinical guidelines recommend routine follow up (RFU) for patients after THA and TKA, with an X-ray and clinical visit within 3 months post-surgery and again at 1 year (5,6). There is currently insufficient high-level evidence to support or challenge the continued use of routine follow-up. The current guidelines for RFU after THA and TKA are based on limited observational data, and randomized controlled trials (RCTs) in this area are rare. A recent NIHR report recommended eliminating RFU before 1 and 10 years in patients with well-functioning implants but did not address the cost-effectiveness or other outcomes relevant to patients associated with RFU 1 year after surgery (7).

Studies show that early follow-up up (FU) to 1 year after surgery results in 0–4.6% detected abnormalities (8,9), of which only a small proportion impacts clinical decision-making and requires additional treatment (10-13). Moreover, in patients indicated for revision surgery, >96.7% present with clinical symptoms such as pain or loss of function. This suggests that early RFU could be safely replaced by check-ups on demand (COD). Registry data also indicate that revisions are rare and typically preceded by symptoms (14-16), bringing the added value of routine follow-up into doubt. Clinical experience further supports the notion that the risk of missed complications is low for asymptomatic patients, which raises the question of whether RFU can be safely de-implemented.

Despite this, eliminating RFU entirely is not without risks. The balance between reducing unnecessary healthcare resource use and ensuring patient safety requires careful consideration. Additionally, patients may find it reassuring to receive confirmation that everything is going well and that they can go back to normal activities, especially as many are not fully recovered at the clinical visit within 3 months post-surgery. Therefore, we suggest a final follow-up within 3 months and then offering COD, as requested by the patient or the healthcare provider (HCP).

The primary objective of this study is to assess whether RFU after THA and TKA can be safely replaced by COD, by comparing the cost-effectiveness of the two approaches 1 year after surgery. The HAKA trial will generate the high-quality evidence necessary to standardize care and guide future clinical practice.

## 2. OBJECTIVES

**Primary Objective:** At 2 years after surgery, what is the effect of a final follow up within 3 months combined with check-ups on demand (COD) compared to routine follow-up (RFU) within 3 months and at 1 year after total hip and knee arthroplasty (THA and TKA) on physical function (effectiveness) and clinical visits (implementation)?

**Secondary Objective(s):** At 2 years after surgery, what is the effect of a final follow up within 3 months combined with COD compared to RFU within 3 months and at 1 year after THA and TKA on complications, surgical interventions, quality of life (QoL), pain and costs.

## 3. STUDY DESIGN

This study has been developed in collaboration with stakeholders, as part of the Zorgevaluatie & Gepast Gebruik (ZE&GG) program. The stakeholders include clinicians, general practitioners, physiotherapists, patient representatives, epidemiologists, a cost-effectiveness expert, health insurers, guideline developers, and implementation experts. During a co-creation phase, multiple meetings were held in which the diverse interests and expertise of these stakeholders were integrated into the study design. Their continued involvement will guide the study's progress and implementation throughout the project.

This is a hybrid effectiveness (de-)implementation trial type II (17), with a stepped-wedge cluster trial design. A total of 10 hospitals will transition from a period with RFU to a period with COD, with a wash-out period (transition) of 2 months. The aim is to gradually de-implement RFU, with all centers eventually using COD as the standard of care. The inclusion period will last 14 months, followed by a 2-year follow-up for each patient. The total duration of data collection will be from July 2025 (first patient inclusion) to August 2028 (last patient, last visit).

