**Table 1. Monthly patient inclusion per center in a stepped wedge design.**

| Period | Center 1                      | Center 2   | Center 3   | Center 4   | Center 5   | Center 6   | Center 7   | Center 8   | Center 9   | Center 10  | Total |            |
|--------|-------------------------------|------------|------------|------------|------------|------------|------------|------------|------------|------------|-------|------------|
|        | Anticipated included patients |            |            |            |            |            |            |            |            |            |       | Cumulative |
| Jul-25 | 4                             | 4          | 4          | 4          | 4          | 4          | 4          | 4          | 4          | 4          | 40    | 40         |
| Aug-25 | 6                             | 6          | 6          | 6          | 6          | 6          | 6          | 6          | 6          | 6          | 60    | 100        |
| Sep-25 | 10                            | 10         | 10         | 10         | 10         | 10         | 10         | 10         | 10         | 10         | 100   | 200        |
| Oct-25 | 10                            | 10         | 10         | 10         | 10         | 10         | 10         | 10         | 10         | 10         | 100   | 300        |
| Nov-25 | Transition                    | Transition | 10         | 10         | 10         | 10         | 10         | 10         | 10         | 10         | 80    | 380        |
| Dec-25 | Transition                    | Transition | Transition | Transition | 10         | 10         | 10         | 10         | 10         | 10         | 60    | 440        |
| Jan-26 | 10                            | 10         | Transition | Transition | Transition | Transition | 10         | 10         | 10         | 10         | 60    | 500        |
| Feb-26 | 10                            | 10         | 10         | 10         | Transition | Transition | Transition | Transition | 10         | 10         | 60    | 560        |
| Mar-26 | 10                            | 10         | 10         | 10         | 10         | 10         | Transition | Transition | Transition | Transition | 60    | 620        |
| Apr-26 | 10                            | 10         | 10         | 10         | 10         | 10         | 10         | 10         | Transition | Transition | 80    | 700        |

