| May-26 | 10                            | 10         | 10         | 10         | 10         | 10         | 10         | 10         | 10         | 10         | 100   | 800        |
| Jun-26 | 10                            | 10         | 10         | 10         | 10         | 10         | 10         | 10         | 10         | 10         | 100   | 900        |
| Jul-26 | 6                             | 6          | 6          | 6          | 6          | 6          | 6          | 6          | 6          | 6          | 60    | 960        |
| Aug-26 | 4                             | 4          | 4          | 4          | 4          | 4          | 4          | 4          | 4          | 4          | 40    | 1000       |
| Total  | 100                           | 100        | 100        | 100        | 100        | 100        | 100        | 100        | 100        | 100        | 1000  |            |

|                          |
|--------------------------|
| Routine follow-up (RFU)  |
| Check-Up On Demand (COD) |

**Note:** The numbers per month represent the inclusion of patients with either THA or TKA, starting with 2 patients per month for each surgery, followed by 3 patients per month, and then 5 patients with THA and 5 patients with TKA per month.

The order in which the ten hospitals transition from RFU to COD will be determined through randomization. Randomization at the center level enhances the study's methodological rigor, reducing potential biases and increasing the generalizability and strength of the evidence. Besides, the study will be nested in the LROI database, which facilitates long term FU to monitor revision surgeries and mortality beyond the current projects timeline, with minimal additional effort.

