## 4. STUDY POPULATION

### 4.1 Population (base)

The study population will consist of patients scheduled for primary Total Hip Arthroplasty (THA) or Total Knee Arthroplasty (TKA) due to osteoarthritis within the Netherlands. This population is drawn from a diverse source population, reflecting the broader demographic characteristics of patients undergoing these procedures in Dutch hospitals.

Patients undergoing THA and TKA are predominantly female, with more than 60% representation for both procedures. The average age of patients is approximately 70 years for THA and 68 years for TKA.

On average, each participating center performs 600 THA and 400 TKA procedures annually.

Given that, there is a high likelihood that the planned recruitment targets will be met. Additionally, the intervention is part of standard care regardless of whether the patient participates in the study, and the study burden for participants is minimal, further increasing the probability of successful recruitment.

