### **10.1 Primary study parameter(s)**

PROMIS physical function will be presented as mean with standard deviation, assuming normality. Differences in PROMIS physical function between the RFU and COD groups will be compared using linear mixed models, with repeated measurements clustered within participants and participants clustered within hospitals (random intercepts). The intervention group (RFU vs. COD), baseline PROMIS physical function, and time points (12, 15, 18 and 24) will be included as fixed effects to determine the crude effect of the intervention at each time point, with the primary outcome at 24 months. Given the stepped wedge design, the duration of the intervention period differs between sites. Therefore “period” is also included as a fixed effect. To assess of the effect of COD might increase over a longer period of time, an interaction term (period \* intervention) will be tested for these possible time effects for the primary outcome.

For healthcare consumption, the percentage of patients who have had at least one clinical visit or X-ray 1 year after RFU or COD will be presented for each group. Additionally, the average number of visits and X-rays per patient will be reported.

A logistic generalized linear mixed model (GLMM) will be used to compare the presence or absence of visits/X-rays (yes/no per patient) between RFU and COD. A Poisson regression analysis will be performed to assess the average number of visits and X-rays per patient, adjusting for potential confounders. Interaction terms between the confounders and the intervention group will also be included to explore whether certain patient characteristics influence the differences in healthcare consumption between RFU and COD.

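### Table 1 staggers two-month wash-outs by only one month, so RFU and COD recruit together in 2 of 14 months; two-month steps would sharpen the PROMIS comparison considerably with the same patients and duration

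*Protocol*

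**What the plan says.** Protocol section 3 states: "A total of 10 hospitals will transition from a period with RFU to a period with COD", "with a wash-out period (transition) of 2 months". It adds: "The inclusion period will last 14 months". Below Table 1 it says: "The order in which the ten hospitals transition from RFU to COD will be determined through randomization".

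Table 1 gives the dates. Pairs of hospitals enter transition in Nov-25, Dec-25, Jan-26, Feb-26 and Mar-26, and no patients are included during a transition. The Mar-26 row ends "Transition | Transition | Transition | Transition | 60 | 620": pairs 4 and 5 are in transition and every recruiting hospital is already on COD. Each hospital's monthly quota is 4, then 6, then 10 for ten months, then 6, then 4. Half are THA and half TKA ("then 5 patients with THA and 5 patients with TKA per month" at full rate).

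Section 10 analyses the two joints separately. Section 10.1 fits PROMIS with random intercepts for participant and hospital and adds period as a fixed effect, for this reason: "Given the stepped wedge design, the duration of the intervention period differs between sites". The protocol does not say how period is coded. Section 4.4 plans 190 evaluable patients per group per joint (250 recruited), with SD 9, a margin of 3, a one-sided 97.5% interval and 90% power.

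**The concern.** A stepped-wedge trial with period in the model learns about the intervention mainly from calendar times when some hospitals are in each condition. Where all recruiting hospitals are in the same condition, the period effect absorbs the level, and those patients serve mainly to estimate hospital differences.

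In Table 1 the transition is longer than the step, so the next pair stops RFU inclusion before the previous pair has begun COD inclusion. This shrinks the overlap to two months. At stake is the precision of the clinical primary endpoint. Nothing in the protocol requires one-month steps, and the 14 months have room for two-month steps with the same wash-out.

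**Working it through.** **1. The plan's own figure.** n per group = 2 × 9² × (1.960 + 1.282)² / 3² = 189.1, so 190. The section 4.4 figure is reproduced. Recruiting 250 with 24% loss leaves 190. The implied standard error (SE) is 9 × √(2/190) = 0.92.

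**2. Overlap, both joints together.** The arm is read from the position before or after the transition.
- Table 1: Jan-26 has 40 RFU and 20 COD; Feb-26 has 20 RFU and 40 COD. The 440 earlier inclusions are all RFU and the 440 later ones all COD. Overlap: 120 of 1000.
- Two-month steps (transitions from Sep-25, Nov-25, Jan-26, Mar-26, May-26), as RFU/COD: Nov and Dec 60/20, Jan and Feb 40/40, Mar and Apr 20/60. Overlap: 6 × 80 = 480 of 1000.
- Each hospital's 14 quotas sum to 120. In both layouts the two transition months each carry a quota of 10, so every hospital includes 100. Both layouts total 500 RFU and 500 COD, or 250 per arm per joint.

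**3. Hand check at ICC 0 with monthly periods.** Only overlap months count, each contributing n₁n₂/(n₁+n₂), per joint at 76% retention.
- Table 1: each month 7.6 × 15.2 / 22.8 = 5.07; two months give 10.13. SE = √(81/10.13) = 2.83.
- Two-month steps: four months at 7.6 × 22.8 / 30.4 = 5.7 and two at 15.2 / 2 = 7.6; total 38.0. SE = √(81/38.0) = 1.46.
- Variance ratio: 38.0 / 10.13 = 3.75.

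**4. With hospital clustering.** Generalised least squares on hospital-month means: V = diag(81(1−ρ)/n) + 81ρ·**11**ᵀ per hospital, fixed period effects, random hospital intercept, and the variance of the COD effect taken from (Σ XᵀV⁻¹X)⁻¹. The protocol gives no ICC (ρ), so 0.001-0.05 is assumed. The chance of showing non-inferiority at a true difference of 0 is Φ(3/SE − 1.96).

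| ICC | SE, Table 1 | SE, two-month steps | Variance ratio | Chance, Table 1 | Chance, two-month steps |
|---|---|---|---|---|---|
| 0.001 | 2.83 | 1.47 | 3.7 | 18% | 53% |
| 0.01 | 2.88 | 1.55 | 3.4 | 18% | 49% |
| 0.05 | 2.93 | 1.71 | 2.9 | 17% | 42% |

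**5. Dependence on the coding of period (ICC 0.001-0.05).**

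| Model | Variance ratio | Chance, Table 1 |
|---|---|---|
| Calendar months | 2.9-3.7 | 17-18% |
| Two-month blocks | 2.6-3.3 | 19-20% |
| Three-month blocks | 2.2-2.7 | 24-25% |
| Months, fixed hospital effects | 2.4 | 16-17% |
| Linear trend | 1.5-1.9 | 32-34% |
| No period term | 0.83-0.99 | about 90% |

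**6. Baseline adjustment.** An assumed adjusted SD of 7.5 gives 23-25% for Table 1 and 56-69% for two-month steps with monthly periods. At a given ICC the variance ratio does not depend on the SD.

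**The case against.** Nothing in section 3 is false or contradictory. One-month steps are a design choice, and the alternative is simply better for one analysis. That is fair: this is an improvement on offer, not an error.

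Three stronger readings are tempting, and the protocol does not support them.
- *A threefold gain is established.* Section 10.1 leaves period undefined, and its stated reason could even suggest time since the switch. The column headed Period in Table 1 lists calendar months, which favours the monthly coding but does not settle it. The gain must be quoted as a range. It does persist under every calendar coding examined that keeps period.
- *Every outcome gains.* Period is named only for PROMIS. The models for visits, X-rays, complications, interventions, quality of life and pain do not list it, and satisfaction has a t test. Without period the new layout is slightly less precise (at ICC 0.05, SE 1.01 against 0.93).
- *Re-spacing repairs the power.* It does not reach 90% under any coding that keeps period. The rest of the shortfall belongs to the individually randomised formula in section 4.4, which is a separate matter.

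The new layout also thins the data at the ends. First-pair RFU and last-pair COD inclusions each fall from 15 to 5 per joint per hospital, about 4 evaluable. The first pair's RFU data would rest wholly on the two start-up months, so a late site opening could remove them. In a de-implementation trial that is a real cost, though small beside the gain in precision.

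**Conclusion.** The point holds for the PROMIS primary analysis. Table 1 has both arms open for only 120 of 1000 inclusions, and two-month steps raise this to 480 with the same patients, quotas, wash-out and duration. With monthly periods the SE per joint falls from about 2.8-2.9 to 1.5-1.7, and the chance of showing non-inferiority at no true difference rises from 17-18% to 42-53%. Across the codings that keep period, the variance ratio runs from 1.5 to 3.7.

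These figures assume SD 9, 190 evaluable per arm per joint, an ICC of 0.001-0.05 and a single 24-month measurement without gain from baseline adjustment. The direction is firm for any outcome whose model includes period; the size depends on the coding. It is a cheap and worthwhile redraw that leaves power short of the plan's target.

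**What to change.** Redraw Table 1 so that the five randomised pairs enter the two-month transition in Sep-25, Nov-25, Jan-26, Mar-26 and May-26. Keep the monthly quotas, the 14 months, 100 patients per hospital and 250 per arm per joint. State in section 10.1 how period is coded, since the size of the gain depends on it.

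The cost is one amended table and new hospital start dates, plus the thinner data in the first and last pairs. The first pair's sites need to open on time.

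If the first switch cannot move, keep the dates and shift quotas towards Jan-26 and Feb-26. For example, per-joint monthly quotas of 2, 3, 3, 3, 3, 5, 15, 15, 5, 3, 3, 3, 3, 2 bring the SE to about 1.75 at ICC 0.01 (1.92 at ICC 0.05), with monthly periods. As written, these give 254 per arm per joint, so 1016 patients in all and 76 to 120 per hospital; they must be rescaled to 1000. Feasibility also needs checking: section 4.1 says "On average, each participating center performs 600 THA and 400 TKA procedures annually", so 15 TKA inclusions would be 15 of about 33 (400/12) TKA procedures in a hospital-month, before eligibility and consent.
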